## Abstract

**Background:**

Pharmacotherapy for common mental disorders is frequently limited by adverse events and suboptimal adherence. While music therapy offers a promising nonpharmacological alternative, its clinical utility is currently constrained by limited accessibility, inconsistent efficacy, and a lack of mechanistic clarity.

**Objective:**

This study aims to describe the development of individualized (receptive) music therapy (IMT), an artificial intelligence (AI)–enabled, neuroscience-guided intervention, and to evaluate its efficacy, safety, and underlying neurobiological mechanisms in adults with major depressive disorder, generalized anxiety disorder, and primary insomnia.

**Methods:**

This multistage research program is being conducted at Peking Union Medical College Hospital and comprises four sequential studies: (1) a cross-sectional pilot study (n=20) to benchmark clinical and electroencephalography features, (2) a prospective cohort study (n=80) evaluating the efficacy and safety of nonindividualized receptive music therapy, (3) a pilot randomized clinical trial (n=300) comparing nonindividualized therapy with IMT over 8 weeks, and (4) a prospective validation study (n=60) of a treatment-response prediction model. Participants include adults aged 18 to 60 years with mild-to-moderate major depressive disorder, generalized anxiety disorder, or primary insomnia, along with healthy controls. In the nonindividualized arm, participants engage in daily 30-minute listening sessions using therapist-curated instrumental tracks designed to regulate mood. In the IMT arm, an AI generation pipeline creates bespoke instrumental tracks based on weekly participant preferences regarding tempo, instrumentation, and emotional valence. To equalize participant–researcher contact across arms and reduce attention and expectation bias, participants in the nonindividualized arm complete a weekly music-experience questionnaire matched in length and timing to the IMT arm’s weekly preference assessment, and treatment credibility and outcome expectancy are measured at baseline in both arms. The primary outcomes are the response rate at 8 weeks (defined as ≥50% reduction in Montgomery-Åsberg Depression Rating Scale [MADRS], Hamilton Anxiety Rating Scale [HAMA], or Pittsburgh Sleep Quality Index [PSQI] scores) and changes in quantitative electroencephalography characteristics. Secondary outcomes include changes in MADRS, HAMA, and PSQI scores from baseline to 8 weeks.

**Results:**

Ethical approval was obtained from the Ethics Review Committee of Peking Union Medical College Hospital (I-24PJ0689). Written informed consent will be obtained from all participants. The recruitment started on May 24, 2024, and the study is expected to be completed by December 2027. Results will be disseminated via peer-reviewed publications, conference presentations, and stakeholder communications. Authorship will follow the International Committee of Medical Journal Editors (ICMJE) criteria. The participant-level dataset will be available upon reasonable request.

**Conclusions:**

This protocol outlines a translational framework designed to address the “therapeutic ceiling” of traditional music therapy. By integrating generative AI with neurophysiological monitoring, this program aims to develop a scalable, precision-medicine approach to mental health care that is both clinically effective and biologically grounded.

## Introduction

Pharmacotherapy remains a cornerstone treatment modality for common mental disorders; however, its long-term efficacy is frequently limited by adverse effects and suboptimal patient adherence [1-3]. Consequently, nonpharmacological interventions have emerged as valuable complementary or alternative therapeutic strategies [4].

Research into music therapy has a long history, during which a coherent theoretical framework and reproducible clinical techniques have gradually evolved [5]. In a seminal definition, Bruscia [6] described music therapy as “a systematic process of intervention wherein the therapist helps the client to promote health, using music experiences and the relationships that develop through them as dynamic forces of change.” As the field has matured, music therapy has expanded beyond receptive listening to encompass recreative and improvisational modalities—active approaches that emphasize participation and creativity. Parallel to this, classification by delivery format has distinguished between individual and group-based care. To date, numerous studies have validated the efficacy and safety of music therapy in improving conditions such as depression [7], anxiety [8], insomnia [9], substance use disorders [10], autism spectrum disorder [11], schizophrenia, and schizophrenia-like disorders [12]. Music therapy has also been shown to enhance cognitive function in patients with Alzheimer disease [13], improve psychological and physical outcomes in patients with cancer [14], and provide comfort in end-of-life care [15].

Investigation into the biological mechanisms of music therapy has identified multiple converging pathways [16]. Music can directly modulate anxiety and stress while functioning as an attentional distractor that reduces ruminative thoughts, thereby promoting positive affect and potentially lowering the risk of relapse associated with negative mood states [17,18]. Neuroendocrine and autonomic effects are also well documented, including reductions in cortisol and favorable changes in heart rate and blood pressure [19-21]. These findings suggest downregulation of hypothalamic-pituitary-adrenal axis activity and restoration of autonomic balance. In patients with insomnia, therapeutic benefits are likely mediated by expectancy effects and classical conditioning, which involve forming an association between presleep music and sleep onset [22,23]. Developmental research on caregiver–infant interaction indicates that early human interaction is imbued with musical features (eg, contour, rhythm, and prosody), providing an ethological foundation for music’s regulatory functions [24]. Furthermore, reward-related mechanisms are implicated. Uplifting music facilitates dopaminergic transmission and modulates limbic circuitry involved in pain and emotion [25-27]. More recently, neuroimaging studies have further elucidated these mechanisms. Resting-state and task-based functional magnetic resonance imaging (MRI) studies have demonstrated that music listening engages widespread cortical and subcortical networks, including the prefrontal cortex, insula, and striatum, with activation patterns that overlap substantially with circuits implicated in mood regulation and reward processing [28,29]. Furthermore, a recent meta-analysis has confirmed that music interventions produce measurable changes in neural connectivity patterns associated with emotional processing [30]. From a clinical psychology perspective, therapeutic change is driven by cognitive, affective, and behavioral factors [31]. Cognitive elements include insight and universalization, while affective elements such as acceptance and altruism contribute to emotional healing. Additionally, prior research has highlighted the mediating role of psychological processes, such as immature defense mechanisms, in the relationship between negative life events and mental disorders [32]. Drawing on psychoanalytic theory, sublimation enables the channeling of emotions through constructive outlets such as art and music [33]. Therefore, music therapy holds the promise of transforming maladaptive defense mechanisms into adaptive ones, offering a unique pathway for psychological healing.

Despite these advances, important limitations of music therapy are increasingly recognized. These notably include restricted access and a “therapeutic ceiling,” whereby conventional music therapy approaches yield moderate but plateauing clinical improvements, beyond which further gains are difficult to achieve using existing methods. Certain active modalities require specialized environments and personnel. Consequently, their availability in routine clinical settings remains limited, and associated costs further constrain uptake. Moreover, effectiveness varies across reports. While recent studies suggest benefits for anxiety and depressive symptoms, comparisons with psychological treatments have shown no significant difference in patient-reported outcomes [7]. Similarly, for insomnia, subjective improvements in sleep quality are often reported, but objective metrics such as total sleep time have demonstrated no significant change in some short-term trials [9].

To address these dual challenges of accessibility and efficacy, we propose a novel approach guided by prior literature and clinical experience: individualized (receptive) music therapy (IMT). This protocol outlines the development of IMT, an artificial intelligence–enabled and neuroscience-guided intervention designed to tailor musical stimuli to patient-specific preferences. We aim to enhance the precision and durability of therapeutic effects in mental health care and to evaluate the efficacy, safety, and mechanisms of action of IMT across multiple stages.

## Methods

### Study Design

The program comprises 4 sequential studies (Table 1 and Figure 1): 1 cross-sectional study, 2 prospective cohort studies, and 1 randomized controlled trial (RCT). The target populations are adults with mild-to-moderate major depressive disorder (MDD), generalized anxiety disorder (GAD), or primary insomnia (PI), as well as healthy controls. All studies use a common assessment framework including baseline demographics, clinical characteristics, symptom severity, and electroencephalography (EEG), with follow-up assessments at weeks 1, 2, 4, 6, and 8.

**Table 1. T1:** Study description of the individualized (receptive) music therapy research program.

Study	Description	Translational role
Study 1 (Cross-sectional)	A pilot study (n=20; 5 per group: MDD^a^, GAD^b^, PI^c^, and HC^d^) to characterize clinical features and EEG^e^ patterns across the target disorders and healthy controls. These findings will be benchmarked against prior literature to calibrate study procedures.	Findings will be used to calibrate assessment procedures, verify the feasibility of EEG protocols, and generate preliminary hypotheses regarding disorder-specific neurophysiological signatures to guide the analytical framework of subsequent studies.
Study 2 (Prospective Cohort)	An open-label evaluation (n=80; 20 per group: MDD, GAD, PI, and HC) of the efficacy and safety of 8-week nonindividualized receptive music therapy with concurrent EEG monitoring.	Establishes preliminary efficacy benchmarks and identifies EEG features associated with treatment response. These data serve as the reference standard against which the added benefit of individualization is evaluated in study 3.
Study 3 (Randomized Controlled Trial)	A pilot RCT^f^ (n=300; MDD, GAD, and PI) in which participants are randomized 1:1 to receive either nonindividualized receptive music therapy or IMT^g^ for 8 weeks.	Provides the first direct comparison of individualized versus nonindividualized approaches. Clinical and EEG data from studies 1‐3 are pooled to develop a treatment-response prediction model.
Study 4 (Prediction Validation)	A prospective cohort study (n=60) in which all participants receive IMT, and the prespecified prediction model derived from studies 1‐3 is applied at baseline to classify participants as predicted responders or nonresponders.	Validates the prediction model in an independent sample. Unlike study 2, which evaluates the nonindividualized intervention, study 4 exclusively administers IMT and focuses on predictive accuracy rather than treatment efficacy.

a MDD: major depressive disorder.

b GAD: generalized anxiety disorder.

c PI: primary insomnia.

d HC: healthy control.

e EEG: electroencephalography.

f RCT: randomized clinical trial.

g IMT: individualized (receptive) music therapy.

**Figure 1. F1:**
[figure not shown]
Study flowchart. MDD: major depressive disorder; GAD: generalized anxiety disorder; PI: primary insomnia; non-indiv: nonindividualized; EEG: electroencephalography.

The 4 studies are designed as a sequential translational pipeline in which each stage builds upon the preceding one. Study 1 serves as an exploratory pilot to calibrate clinical and EEG assessment procedures, verify protocol feasibility, and generate preliminary hypotheses regarding disorder-specific neurophysiological features. Although the sample size (n=20) is insufficient for definitive biomarker identification, this study provides essential groundwork for refining the measurement framework used in subsequent stages. Study 2 then evaluates the efficacy and safety of nonindividualized receptive music therapy in a larger cohort, establishing the clinical and neurophysiological benchmarks against which the individualized intervention will be compared. Study 3 directly compares the 2 approaches in a randomized controlled framework, enabling assessment of the incremental benefit of AI-enabled personalization. Finally, study 4 validates a treatment-response prediction model developed from the cumulative data of studies 1 through 3; this study is distinct from study 2 in that all participants receive IMT and the primary objective is to evaluate predictive accuracy rather than treatment efficacy per se.

### Recruitment

Participants are recruited at Peking Union Medical College Hospital via clinician referral and community outreach. Inclusion criteria for the MDD, GAD, and PI groups are as follows: (1) age 18 to 60 years; (2) diagnosis of the relevant disorder according to the *Diagnostic and Statistical Manual of Mental Disorders, Fifth Edition* (*DSM-5*) criteria; (3) severity scores within prespecified ranges (MDD: Hamilton Depression Rating Scale 17-item version [HAMD-17] score>7 and ≤23; GAD: HAMA score>7 and ≤21) or, for PI, mild-to-moderate severity with predominant sleep-onset difficulty persisting longer than 3 months; and (4) capacity to provide written informed consent. Exclusion criteria include the following: (1) any current or lifetime history of comorbid mental disorders, such as bipolar disorder, obsessive-compulsive disorder, or substance use disorder; (2) severe or unstable medical conditions; (3) pregnancy or lactation; and (4) sensory or cognitive impairments, such as hearing loss or intellectual disability, that would preclude participation.

The use of the HAMD-17 for screening and the MADRS for outcome assessment reflects the complementary psychometric properties of these instruments. The HAMD-17 is widely used as a screening and severity-grading instrument in clinical practice and provides well-established severity thresholds for defining mild-to-moderate depression. The MADRS, by contrast, offers superior sensitivity to change over time and is recommended as a primary outcome measure in clinical trials owing to its focus on core depressive symptoms and reduced somatic item content, which minimizes confounding by physical comorbidities [34].

### Concomitant Treatments

During the study period, the use of any psychotropic medications or other treatments for the target disorder is prohibited in principle, including psychotherapy and neuromodulation therapies (eg, transcranial magnetic stimulation). Medications for the management of treatment-emergent adverse events are permitted. Any concomitant medications or treatments used during the study, including those administered inadvertently, are documented in the case report forms, with details of drug name, dosage, dates of administration, and indication recorded at each visit. Participants who require initiation of prohibited treatments owing to clinical deterioration will be withdrawn from the study and will receive appropriate clinical care.

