### Treatment-Response Prediction Model

The treatment-response prediction model to be validated in study 4 will be developed using data from studies 1 through 3. Candidate predictors will include baseline demographic characteristics (age, sex, and education), clinical variables (baseline symptom severity scores, disorder diagnosis, duration of illness, and medication status), music preference profiles (STOMP-R scores), and baseline neurophysiological features (resting-state EEG spectral power and frontal alpha asymmetry). The outcome variable for model development will be treatment response at 8 weeks, defined as a reduction of 50% or greater in the disorder-specific primary outcome measure. Model development will use logistic regression with regularization (elastic net) to handle the potentially large number of candidate predictors relative to the sample size, with internal validation using 10-fold cross-validation. The final model will be prespecified and locked before its application to the study 4 validation cohort. Model performance in study 4 will be assessed using discrimination metrics (area under the receiver operating characteristic curve, sensitivity, and specificity) and calibration measures (Hosmer–Lemeshow test and calibration plots). Should the cumulative sample from studies 1 through 3 prove insufficient for robust model development, alternative approaches such as penalized regression or decision-tree methods will be considered, and the model validation in study 4 will be framed accordingly. A detailed statistical analysis plan for the prediction model will be finalized before study 4 enrollment commences.

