### Outcome Measures

#### Primary Outcome Measure

Response rate at 8 weeks, defined as ≥50% reduction in MADRS, HAMA, or PSQI scores; change in quantitative EEG characteristics from baseline to week 8. Specific EEG features of interest are detailed in the statistical analysis plan.

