#### Primary Outcome Analysis

For the response rate at 8 weeks, between-group comparisons will be conducted using chi-square tests, with results reported as risk difference and risk ratio with corresponding 95% CIs. To accommodate the repeated-measures structure of the data (assessments at baseline and at weeks 1, 2, 4, 6, and 8), linear mixed-effects models for repeated measures (MMRM) will be used for continuous outcomes, with fixed effects for treatment group, time, and their interaction; baseline scores will be included as covariates; and random intercepts for participants will be specified to accommodate within-subject correlation. Because study 3 cannot blind participants and the IMT arm involves additional engagement, 2 prespecified sensitivity analyses will probe the robustness of the primary treatment effect to expectation and attention effects: (1) the MMRM and the response-rate models will be refitted with baseline CEQ scores added as covariates; and (2) the analyses will be repeated with adjustment for the Bang Blinding Index to explore whether the estimated treatment effect is attenuated after accounting for residual unblinding. Concordance between the primary (unadjusted) and these expectancy-adjusted estimates will be interpreted as evidence regarding the extent to which any observed benefit is attributable to personalization of the stimulus rather than to differential expectancy or attention. Time to response or remission will be compared between groups using Kaplan–Meier survival curves and the log-rank test. For study 3, the primary analysis will follow an intention-to-treat principle, including all randomized participants according to their assigned group. A supplementary per-protocol analysis will include only participants who complete at least 80% of scheduled listening sessions (ie, a minimum of 45 of 56 daily sessions).

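### The plan does not say whether permitted adverse-event medication includes psychotropics, and its per-protocol set, defined by listening alone, keeps participants who received prohibited treatment

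*Protocol article*

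**What the plan says.** The rules on other treatment are in the Concomitant Treatments section of the protocol article, in four steps.

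- Prohibition: "the use of any psychotropic medications or other treatments for the target disorder is prohibited in principle". Psychotherapy and neuromodulation are included.
- Allowance: "Medications for the management of treatment-emergent adverse events are permitted". No drug class is named or excluded.
- Recording: "Any concomitant medications or treatments used during the study, including those administered inadvertently, are documented in the case report forms". Drug, dates and indication are taken at each visit. No consequence for the analysis is attached.
- Withdrawal: "Participants who require initiation of prohibited treatments owing to clinical deterioration will be withdrawn from the study".

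The outcome and analysis sets are defined elsewhere. Primary Outcome Measure gives "Response rate at 8 weeks, defined as ≥50% reduction in MADRS, HAMA, or PSQI scores", with no condition on other treatment. Under Primary Outcome Analysis, for study 3, "the primary analysis will follow an intention-to-treat principle, including all randomized participants according to their assigned group". The same section adds: "A supplementary per-protocol analysis will include only participants who complete at least 80% of scheduled listening sessions". Intervention Fidelity and Adherence Monitoring uses the same threshold, 45 of 56 sessions, to decide who is nonadherent for the per-protocol analysis. Neither section mentions concomitant treatment.

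**The concern.** Study 3 enrols people with depression, generalized anxiety or insomnia. New or worse anxiety, agitation or sleeplessness during the 8 weeks can be described as a treatment-emergent adverse event or as deterioration of the target disorder. The article does not say which description applies, or whether the adverse-event allowance reaches psychotropics. Two participants with the same symptoms and the same drug could be handled differently: one stays and is scored at week 8, while the other is withdrawn and may have no week-8 score, so that the outcome is imputed under the Missing Data section.

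The second problem follows from a rule that the plan does state. A per-protocol analysis should show the effect among those treated as the protocol intends. Here the set is defined by listening sessions, while the main restriction on other treatment plays no part. Someone who took a prohibited drug inadvertently, or received a psychotropic as adverse-event medication, and who listened to 45 or more sessions, is kept. If the per-protocol result agrees with the primary result, that agreement says nothing about the influence of other treatment.

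**Working it through.** The plan gives no figure on this point to reproduce, so the check is mainly a comparison of sections. The arithmetic only shows scale.

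**Step 1: paths for one event.** Take worsening anxiety or insomnia for which a psychotropic is started.

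| Label given to the event | Sentence that applies | Result |
|---|---|---|
| Clinical deterioration | Withdrawal | Leaves the study |
| Adverse event, allowance read to include psychotropics | Allowance | Stays, scored at week 8 |
| Adverse event, allowance read to exclude psychotropics | Prohibition | Barred, but the stated withdrawal trigger is deterioration, so no consequence is given |
| Inadvertent use | Recording | Recorded, no consequence given |

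Nothing in the article chooses between the rows. The Treatment-Response Prediction Model section lists "duration of illness, and medication status" among candidate predictors, so some variation in medication seems to be foreseen, although it does not say which drugs or when.

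**Step 2: per-protocol set.** The threshold is 0.80 × 56 = 44.8, rounded up to 45 sessions, as stated. Apart from withdrawal, nothing in the definition removes a person in any of the four rows. Those who stay and listen to 45 sessions are in.

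**Step 3: scale of the scoring choice.** Let m be the share of an arm medicated and retained, and r their response rate. The article gives neither. I take m from 2% to 15% and r = 70%, borrowed from the control rate in Sample Size Calculation.

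Arm rate if scored as observed, minus arm rate if scored as nonresponse = m × r:
- m = 2%: 0.02 × 0.70 = 1.4 points
- m = 5%: 0.05 × 0.70 = 3.5 points
- m = 10%: 0.10 × 0.70 = 7.0 points
- m = 15%: 0.15 × 0.70 = 10.5 points

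With r from 50% to 90%, the range is 0.02 × 0.50 = 1.0 to 0.15 × 0.90 = 13.5 points.

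Shift in the arm difference = r × (m in IMT − m in control):
- 10% against 5%: 0.70 × 0.05 = +3.5 points
- 15% against 5%: 0.70 × 0.10 = +7.0 points
- 5% against 10%: 0.70 × (−0.05) = −3.5 points
- equal use: 0

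The article's threshold for clinical importance is 20 points.

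**Step 4: scale of the per-protocol exclusion.** Keeping a share m with response r, when the other members respond at r0, shifts the set's rate by m × (r − r0). With r0 = 70% and m = 10%, r = 90% gives 0.10 × 0.20 = +2.0 points, r = 50% gives −2.0 points, and r = 70% gives 0. At m = 5% the extremes are ±1.0 point. The exclusion therefore moves the estimate less than the scoring choice in step 3 does.

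**The case against.** A reader might infer that the section contradicts itself outright, banning psychotropics in one sentence and permitting them in the next. The text does not go that far. The allowance never mentions psychotropics, and after an explicit ban it can be read as covering other drugs only. Worsening that needs target-disorder treatment can likewise be read as deterioration, which has a single path. That leaves an undefined boundary, which the qualifier in the prohibition makes looser, but not a contradiction.

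A reader might also infer that the primary analysis wrongly credits drug effects to the music and biases the IMT comparison. The documents do not support this. No sentence says that medicated participants count as responders; it follows only from the absence of a rule, and the statistical analysis plan is not shown. Scoring everyone as observed at week 8 is a legitimate treatment-policy reading of the stated intention-to-treat analysis. Counting any use as nonresponse answers a different question, and a single inadvertent dose would then decide a participant's outcome. Bias in the comparison needs unequal use. The article does not say who labels events or whether they know the arm, and outcome assessors are blinded.

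On the per-protocol set, it is fair to say that the wording gives a necessary condition and that further exclusions could be listed in the analysis plan. But the article defines the set in two places with one criterion each time, and a person who applies that definition keeps users of prohibited treatment. The conduct rule is also applied while the trial runs, and a later analysis plan cannot undo inconsistent withdrawals. These two parts stand.

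**Conclusion.** The point holds in limited form. The sentences on prohibition, adverse-event medication and withdrawal overlap without a stated boundary, so the same event can lead to staying or leaving. The per-protocol set, as defined, includes participants who received prohibited treatment, which defeats part of its purpose.

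The size is unknown because the article gives no rate of use. The figures of 3.5 to 7.0 points for one arm rest on assumed use of 5% to 10% and an assumed 70% response among users. They measure the gap between two scoring rules and not a bias against a true effect. With equal use the arm difference does not move, and the largest between-arm shift illustrated, 7.0 points, is below the 20-point threshold. This does not show a flaw in the primary analysis. It is a gap in a conduct rule and a defect in a supplementary analysis, and both are easy to repair.

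**What to change.** 1. In Concomitant Treatments, reconcile the sentences so that any one event leads to one path, and say whether the adverse-event allowance includes psychotropics. Which path applies is for the investigators.
2. In Intervention Fidelity and Adherence Monitoring and in Primary Outcome Analysis, add to the per-protocol definition that participants with any recorded post-baseline psychotropic or other target-disorder treatment are excluded, whatever the recorded indication and including inadvertent use.
3. Report such use by arm.
4. Keep the intention-to-treat analysis as primary. Scoring users as nonresponders should be a sensitivity analysis at most.

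The cost is wording. The data needed are already recorded at each visit. The downside is a slightly smaller per-protocol set.

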### Sample Size Calculation

Study 3 is a pilot RCT designed to assess feasibility and to generate preliminary effect estimates to inform a definitive future trial. Accordingly, the sample size is based on precision estimation rather than formal power calculation. The primary outcome is the response rate at 8 weeks, defined as a reduction of 50% or greater from baseline in the disorder-specific symptom severity score. We adopted a minimal clinically important difference–anchored CI approach, setting a 20-percentage-point absolute difference in response rates as the threshold for clinical importance. With 50 participants per arm within each diagnostic group, the expected 1-sided 80% CI half-width for the between-group difference in response rates is approximately 8 to 12 percentage points (derived from a response rate of 70% for the control group and a range of between-group differences from 0% to 30%), thereby permitting precise estimation of feasibility metrics and preliminary efficacy signals to plan the definitive trial.

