### Intervention Fidelity and Adherence Monitoring

Several measures are implemented to ensure intervention fidelity and to monitor participant adherence. Daily listening compliance is tracked automatically through the custom-developed mobile app, which records session initiation time, duration of playback, and completion status for each listening session. Adequate adherence is defined a priori as completion of at least 80% of scheduled listening sessions (ie, a minimum of 45 of 56 daily sessions over the 8-week intervention period). Participants falling below this threshold will be classified as nonadherent for the purpose of per-protocol analysis, although all randomized participants will be included in the primary intention-to-treat analysis regardless of adherence level. To ensure the quality and consistency of AI-generated music in the IMT arm, a 2-stage quality assurance process is used. First, all generated tracks are screened against predefined acoustic parameters (as described above) to exclude those falling outside acceptable ranges. Second, a certified music therapist reviews a random sample of generated tracks each week (approximately 20% of total output) to verify that the musical content is therapeutically appropriate, free of unexpected artifacts, and consistent with the intended affective trajectory. Any quality concerns are flagged and addressed before participant delivery. For the nonindividualized arm, intervention fidelity is maintained using a standardized track library curated by the same certified music therapist, with track selection following the predefined affective trajectory protocols. Session delivery is identical across both arms in terms of duration, frequency, and environmental instructions.

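### The supplementary per-protocol set is defined by listening sessions alone, so some users of prohibited treatment still qualify and the recorded use enters no stated analysis

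*Protocol article*

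**What the plan says.** Concomitant Treatments sets the condition: "the use of any psychotropic medications or other treatments for the target disorder is prohibited in principle, including psychotherapy and neuromodulation therapies". It expects breaches and has them recorded: "Any concomitant medications or treatments used during the study, including those administered inadvertently, are documented in the case report forms", with drug, dosage, dates and indication taken at each visit. One consequence is stated, and only for one kind of user: "Participants who require initiation of prohibited treatments owing to clinical deterioration will be withdrawn from the study".

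Intervention Fidelity and Adherence Monitoring defines adequate adherence as "completion of at least 80% of scheduled listening sessions (ie, a minimum of 45 of 56 daily sessions over the 8-week intervention period" and continues: "Participants falling below this threshold will be classified as nonadherent for the purpose of per-protocol analysis". Primary Outcome Analysis repeats the single criterion: "A supplementary per-protocol analysis will include only participants who complete at least 80% of scheduled listening sessions". The primary analysis is kept separate from this: "all randomized participants will be included in the primary intention-to-treat analysis regardless of adherence level".

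**The concern.** A participant can complete 45 sessions while also receiving psychotherapy or a psychotropic drug. The article forbids that combination and records it, yet its per-protocol definition does not look at it. The intention-to-treat analysis rightly keeps such participants. If the per-protocol set keeps them too, both analyses carry the same co-treatment, and agreement between them says nothing about whether co-treatment influenced the result.

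Participants in study 3 are not blinded, so use could plausibly differ between arms, although the article gives no figures. With unequal use, the per-protocol difference in response rates could shift in either direction. With equal use, a real difference would be diluted.

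**Working it through.** **1. The stated threshold.** 8 weeks x 7 daily sessions = 56. 0.80 x 56 = 44.8, rounded up to 45. 45/56 = 80.4% and 44/56 = 78.6%, so 45 of 56 reproduces.

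**2. Who is removed by the stated rules, and who is not.** At one session a day, the 45th session cannot be reached before day 45. By the week 6 visit the maximum is 6 x 7 = 42.

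- Withdrawn for deterioration before the 45th session: at most 44 sessions, so outside the per-protocol set.
- Starts a prohibited treatment after the 45th session (up to 56 - 45 = 11 days remain): meets the criterion, even if then withdrawn.
- Uses a prohibited treatment inadvertently, or without deterioration, and keeps listening: meets the criterion.

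No stated rule removes the last two groups.

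**3. Whether another analysis uses the records.** The sensitivity analyses listed for study 3 cover expectancy scores, the blinding index, last observation carried forward, missing-not-at-random and tipping-point scenarios, and trajectory type. None uses on-study concomitant treatment. Medication status appears in the prediction-model section, but as a candidate predictor there and not in the comparison of arms.

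**4. Scale, by illustration only.** The article gives no expected rate of prohibited use. Let p1 and p0 be the response rates without other treatment in the IMT and control arms, f1 and f0 the shares of users among those analysed, and r the response rate in users. The shift in the per-protocol risk difference (IMT minus control) is

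f1 x (r - p1) - f0 x (r - p0).

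The 70% control rate comes from Sample Size Calculation. All values of f1, f0 and r are assumptions.

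- p1 = p0 = 70%, r = 90%, f1 = 5%, f0 = 15%: 0.05 x 0.20 - 0.15 x 0.20 = -2.0 points (71.0% vs 73.0%).
- p1 = p0 = 70%, r = 100%, f1 = 0, f0 = 20%: -0.20 x 0.30 = -6.0 points.
- p1 = p0 = 70%, r = 50%, f1 = 0, f0 = 20%: -0.20 x (-0.20) = +4.0 points.
- Equal use f in both arms: the shift reduces to f x (p0 - p1). It is 0 when the arms respond equally. With p1 = 90% and p0 = 70% it is -1.0 point at f = 5% and -2.0 points at f = 10%.

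The combinations tried (f1 from 0 to 10%, f0 from 5% to 20%, r from 50% to 100%, p1 of 70% or 90%) gave shifts from -6 to +4 points.

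**5. Whether exclusion removes the bias.** The formula treats users and non-users as having the same prognosis. Assume instead that users would respond at 40% untreated and 70% when treated, that response without other treatment is 70% overall in both arms, and that use is 15% in control and 5% in IMT. The true difference is 0.

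- Non-users, control: (0.70 - 0.15 x 0.40)/0.85 = 75.3%. Non-users, IMT: (0.70 - 0.05 x 0.40)/0.95 = 71.6%.
- Users kept: control 0.64 + 0.15 x 0.70 = 74.5%; IMT 0.68 + 0.05 x 0.70 = 71.5%; difference -3.0 points.
- Users excluded: 71.6% - 75.3% = -3.7 points.

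Here exclusion makes the bias slightly larger.

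**The case against.** The best defence is that the list of deviations excluding a participant from a per-protocol set is ordinarily left to the statistical analysis plan, which the article says will be finalized before database lock. Requiring 80% of sessions can be read as a necessary condition only, so a plan that added prohibited treatment would contradict nothing. That reading is possible. But the article does not leave the set open: it gives the definition in two sections, both times with the same single criterion. The point rests on that stated definition, not on silence.

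A reader might infer that every participant with documented prohibited treatment stays in the set. The documents do not support this, because deterioration cases withdrawn before the 45th session drop out by count. Nor does the text say that other users remain in the study; it states no consequence for them.

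A reader might also take the per-protocol analysis as the declared check on the intention-to-treat result. The article calls it supplementary and gives no such purpose.

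Two further objections stand. Any figure for the bias depends on assumed rates of use, and shifts of a few points are small against the precision available: at 150 per arm and 70% response, the pooled 95% half-width is 1.96 x sqrt(2 x 0.21/150) = 10.4 points. And excluding users conditions on one more event after randomization, which, as shown above, need not reduce bias.

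**Conclusion.** The point holds in limited form. The stated per-protocol definition does not match a protocol condition that the same article sets and records. Inadvertent users, users without deterioration who keep listening, and those who start after session 45 all qualify, and their records are used in no stated analysis.

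The consequence is modest. Only a supplementary analysis is affected. The size of any bias cannot be derived from the documents; a range of about -6 to +4 percentage points follows from assumed use rates and assumed response among users. It would be too strong to say that the study 3 result is biased by a known amount, or that excluding users would yield the unbiased effect. The documents give no rate of use, and the direction of selection is unknown.

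**What to change.** In Intervention Fidelity and Adherence Monitoring and in Primary Outcome Analysis, define the per-protocol set as participants who complete at least 45 of 56 sessions and have no documented prohibited treatment, as listed under Concomitant Treatments, between randomization and the week 8 rating. Classify this from the case report forms before unblinding and database lock. Report the number excluded by arm and by reason. Show the session-only result next to it as a sensitivity analysis, so that readers can see how far the estimate depends on the added exclusion. Keep intention-to-treat primary.

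The cost is analysis wording, one classification step and one extra analysis; the data are already being collected and no clinical rule changes. The drawback is a somewhat smaller supplementary set, selected on a further post-randomization event. Counts by arm make that selection visible but do not remove it.
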